### Sample size

The sample size is calculated on the primary outcome by *a priori* analysis in G*Power, version 3.1.9.7 (The G*Power Team, Düsseldorf, Germany). Based on the study design and assumptions, the estimated results suggest that participants who receive a single session of active tDCS or hf-tRNS will demonstrate an improvement in TEXT reading accuracy compared to their baseline performance. On the other hand, participants who receive a single session of sham tDCS or sham tRNS are not expected to show a significant change in their performance compared to baseline. While the design of this project has never been employed in DD, we will refer to (i) a previous study by Costanzo and collaborators (16) who prove the effectiveness of a one-session active left anodal/right cathodal tDCS over temporo-parietal regions in a within-subject design; (ii) a study with similar features (e.g., one-session, sham-controlled experiment, comparing baseline vs. tDCS vs. tRNS vs. sham) assessing other cognitive functions (35).

Based on these previous results, to be cautious and conservative, we estimate a medium effect size (f) of 0.25. With an estimated *f* = 0.25, α value = 0.05 (i.e., probability of false positives of 5%), and *β* = 0.80 (i.e., at least 80% power), the sample size is 24 as calculated using a Repeated Measures-Analysis of Variance (RM-ANOVA) model with four within factors (i.e., baseline, active tDCS, active hf-tRNS, and sham).

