### Statistical analyses and expected results

The Shapiro–Wilk test will be used to test the normality of the data and Levene’s test for the homogeneity of variances. When data will be normally distributed and the assumption of homogeneity will not be violated, parametric analyses will be computed. When one assumption will not be met, non-parametric tests will be conducted or a log-transformation of the distribution will be applied. Sphericity will be verified by Mauchly’s sphericity test and when not met, Greenhouse–Geisser correction will be applied.

Chi-Square analyses will be used to compare the groups on demographic and safety and blinding measures (categorical variables).

Covarying for age, a preliminary analysis to test the effect of the four repetitions (Day 0, Day 1, Day 2, and Day 3) of the reading tasks (accuracy and speed of TEXT, HF, LF, and NW) will be conducted.

RM-ANOVA will be used to compare reading measures (TEXT, HF, LF, and NW accuracy and speed), separately, with conditions (Day 0, A, B, C) as a within-subjects factor and age as covariate.

*Post hoc* comparisons will be assessed using Tukey’s honest significance test.

Partial eta squares (η_p_^2^) will be used as measures of effect sizes.

We hypothesize that:

hf-tRNS will be at least as effective as tDCS in improving TEXT reading accuracy compared with sham condition (primary outcome);hf-tRNS and tDCS will improve performance in the remaining reading tasks (TEXT reading speed and HF, LF, and NW reading accuracy and speed) compared with sham condition;hf-tRNS and tDCS will be as safe as sham condition (i.e., neither tDCS nor hf-tRNS will induce severe AEs or lead to dropouts due to intolerance to stimulation);the blinding will be kept across the conditions.

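### Tukey's test on the four-level factor makes the two planned active-versus-sham comparisons of TEXT accuracy pay for six pairs, a valid choice that costs power at N = 24

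*Protocol article*

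**What the plan says.** Statistical analyses and expected results: each reading measure is analysed by RM-ANOVA "with conditions (Day 0, A, B, C) as a within-subjects factor and age as covariate", and post hoc "comparisons will be assessed using Tukey’s honest significance test". The hypothesis marked as primary in the same section is that "hf-tRNS will be at least as effective as tDCS in improving TEXT reading accuracy compared with sham condition (primary outcome"). The other efficacy hypothesis there compares both techniques with sham on the remaining reading measures.

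Reading tasks: the primary outcome is the change in TEXT accuracy from Day 0 in each active session, compared with the sham session.

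Sample size: "we estimate a medium effect size (f) of 0.25", with alpha 0.05 and "i.e., at least 80% power"; "the sample size is 24 as calculated using" an RM-ANOVA "model with four within factors (i.e., baseline, active tDCS, active hf-tRNS, and sham"). The same section expects both active conditions to improve on baseline and sham not to change. It states neither a correlation between measurements nor a sphericity correction.

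**The concern.** The comparisons that decide the primary outcome, tDCS versus sham and hf-tRNS versus sham, are fixed in advance. The plan nevertheless handles them as post hoc and adjusts them as two of six. The six are three pairs with Day 0 and three among the stimulation conditions. Day 0 is the screening visit and is not part of the randomised order.

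The primary outcome does not need the Day 0 pairs. Each child has one Day 0 value, so (active − Day 0) − (sham − Day 0) = active − sham.

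In a trial of 24 children, unneeded adjustment comes straight off the chance of a clear result. A reader of the sample size section would also take the primary outcome to have 80% power, although that figure belongs to the overall four-level F test.

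**Working it through.** **Inputs.** From the protocol: N = 24, f = 0.25, alpha 0.05, four measurements per child. The calculation uses 24 completers, because the withdrawal section provides for replacement. Assumed: correlation 0.5 (range below), sphericity, two-sided tests, age left out.

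**1. The plan's own figure.** For the within-subject F test, λ = f²·N·m/(1 − ρ) = 0.0625 × 24 × 4 / 0.5 = 12, with 3 and 3 × 23 = 69 df. Power is 81.7% at N = 24 and 79.7% at N = 23, so 24 is reproduced. Other correlations give a different N: 32 at 0.3 and 15 at 0.7.

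**2. The effect on the sham contrasts.** The expected pattern (Day 0, tDCS, hf-tRNS, sham) is (0, d, d, 0). Its grand mean is d/2 and every deviation is ±d/2, so f = d/2 and d = 0.5 SD. The SD of a within-child difference is √(2(1 − 0.5)) = 1 SD. The noncentrality of each active-sham t is therefore 0.5 × √24 = 2.45.

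**3. Critical values of |t|.**
- Tukey, four levels, 69 df: q/√2 = 2.633
- Tukey, three levels, 46 df: 2.422 (2.395 if the 69-df error is kept)
- Dunnett, two contrasts, 69 df: 2.256
- Holm, two contrasts, 69 df: 2.291, then 1.995

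**4. Power at correlation 0.5** (simulated)

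| Procedure | Each active-sham contrast | Both |
|---|---|---|
| Tukey, six pairs (as planned) | 43% | 27% |
| Tukey on tDCS, hf-tRNS, sham only | 52% | 36% |
| Dunnett, two contrasts | 58% | 42% |
| Holm, two paired t tests (23 df) | 59% | 48% |
| Holm, two contrasts, pooled error | – | 51% |

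For at least one contrast, six-pair Tukey gives 59% and paired Holm 70%.

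**5. Splitting the gain.** Removing only the three Day 0 pairs takes the figure for both from 27% to about 36%, or 9 points. The further rise to 48–51% comes from also taking hf-tRNS versus tDCS out of the family and stepping down with Holm. It is not produced by a different error term, since paired tests give slightly less than the pooled error (48% against 51%).

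**6. Range over the unstated correlation** (both contrasts, d = 0.5 SD)

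| Correlation | Tukey, six pairs | Tukey, three pairs | Holm, paired |
|---|---|---|---|
| 0.3 | 16% | 22% | 32% |
| 0.5 | 27% | 36% | 48% |
| 0.7 | 56% | 65% | 75% |

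The levels move a great deal and the ordering does not. The Day 0 pairs cost 6 to 9 points across this range.

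**The case against.** Tukey's test is a valid, conservative follow-up to the RM-ANOVA that the plan names. No error rate is inflated, and the choice of a smaller family is one of efficiency. That stands, and it sets the weight of this point. Contrast-level detail is often left to an analysis plan, but here the protocol itself names the four levels and the test, which together fix the six-pair family.

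A reader might infer that the document makes no use of the Day 0 pairs at all. That goes too far. The sample size section expects improvement over baseline in both active conditions and no change under sham, and the primary outcome is worded against Day 0. What holds is narrower: the listed hypotheses do not test those pairs, the sample size section mentions them only as expectations, and Day 0 drops out of the active-minus-sham contrast.

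It can also be objected that hf-tRNS versus tDCS belongs in the family, because the primary hypothesis names it. This is fair. A family of the three randomised conditions gives 36% for both sham contrasts, not 48%.

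Finally, the plan does not say that both active-sham contrasts must succeed. The figures for both are one way to read success; the per-contrast and at-least-one figures show a smaller relative loss in the same direction.

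**Conclusion.** The point holds as a loss of power and a mismatch between the adjusted family and the listed hypotheses. Under the plan's effect size and an assumed correlation of 0.5, each active-sham comparison has about 43% power, and both together about 27%. Restricting Tukey to the randomised conditions gives about 52% and 36%. Pre-specifying the two sham contrasts gives 42% to 51% for both, depending on the method.

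One might be tempted to blame the Day 0 pairs for the whole gap between 27% and 48%. The calculation does not support that: they account for about 9 points, and the rest follows from the smaller family and the step-down procedure.

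All figures rest on the (0, 0.5, 0.5, 0) pattern, sphericity and 24 completers. The correlation is an assumption of this check, chosen because it reproduces N = 24; the protocol does not state it. The change is worth making because it needs no extra child or visit.

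**What to change.** Name tDCS versus sham and hf-tRNS versus sham on TEXT accuracy as the two pre-specified primary tests. Adjust them by Holm or Dunnett at a familywise 5%, and do not make them conditional on a significant four-level F test. Report hf-tRNS versus tDCS as an estimate with its confidence interval. If a test of that pair is wanted inside the family, use Tukey on the three randomised conditions only. Present Day 0 comparisons descriptively.

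The cost is analysis wording. The Day 0 pairs lose their familywise-adjusted p-values. Under the two-contrast version so does hf-tRNS versus tDCS, which matters because the primary hypothesis names it; the authors should choose between the two versions knowingly. The sample size section should also say that its 80% refers to the overall F test, and state the correlation it used.

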**Discussion:**

We hypothesize that tRNS will demonstrate comparable effectiveness to tDCS in improving reading compared to sham conditions. Additionally, we anticipate that hf-tRNS will exhibit a similar safety profile to tDCS. This study will contribute novel insights into the effectiveness of hf-tRNS, expediting the validation of brain-based treatments for DD.

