Both tDCS and tRNS are considered highly promising tES techniques for the pediatric population due to their favorable safety profile, high tolerability, versatility, ease of use, and low cost (26, 38–43). Interestingly, concerning safety and feasibility, both neurophysiological and behavioral studies [respectively (26, 36, 38)] showed that tRNS has higher skin perception thresholds, lower response rates to adverse events, and more effective blinding, making it a preferable option for the pediatric population.

The current study aims to investigate whether hf-tRNS is effective in improving reading abilities and whether it may outperform tDCS in specific reading aspects. The main goal is to compare the effects of a single online session of hf-tRNS, tDCS, and sham stimulation on text, word, and non-word reading accuracy and speed in children and adolescents with DD. This proof-of-concept study will also assess the safety, tolerability, and blinding parameters of both tES techniques and compare them.

If hf-tRNS proves to be at least as effective as tDCS in improving reading outcomes, these results would provide valuable insights for the development of multi-session hf-tRNS protocols as a potential treatment approach for individuals with DD.

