Concerning reading speed, syllables per seconds (syll/s) will be considered by dividing the total number of pronounced syllables by the time taken to complete the reading task (in seconds) for all tasks (TEXT, HF, LF, NW).

To ensure that the six versions of each reading task (TEXT, HF, LF, and NW) are comparable in terms of difficulty for both accuracy and speed, a pilot study was conducted with a group of typically developing readers. This preliminary investigation helped determine that the task versions will be appropriately matched in difficulty across the different conditions (see Supplementary materials S3).

The primary outcome of the study will be the changes in TEXT reading accuracy during the active tDCS and active hf-tRNS sessions compared to the sham session (tDCS/tRNS), in comparison to the baseline measurement on Day 0. The primary outcome has been defined based on the results of Costanzo et al. (16), whereby a single session of active left anodal/right cathodal tDCS over temporo-parietal regions led to significant improvements on TEXT reading accuracy compared to control conditions.

Similarly, the secondary outcomes of the study will examine changes in TEXT reading speed, as well as changes in the accuracy and speed of the other reading tasks (HF, LF, and NW) during the active tDCS and active hf-tRNS sessions compared to the sham session (tDCS/tRNS), in comparison to the baseline measurement on Day 0.

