## Conclusion

In conclusion, the present study could provide new insights regarding the effectiveness of a newly-wave tES method never used in children and adolescents with DD, the hf-tRNS, potentially paving the way for further studies involving multiple hf-tRNS sessions. Considering the absence of studies evaluating the efficacy of hf-tRNS in improving reading skills and comparing it with the effects obtained with tDCS, we preferred to be cautious in advancing hypotheses of superiority of one technique over the other. However, while expecting comparable effects of the two techniques on outcome measures, we believe that this study may help optimize neuromodulation protocols for dyslexia in the future, for example, by considering the magnitude of the effects obtained by the two techniques. Of importance, this project will employ an experimental design that keeps the study burden for DD participants at a minimum, while providing key steps to understand which tES technique may be most effective for multi-session treatment applications.

The opportunity to compare tDCS and hf-tRNS in the same experimental setting, investigating whether differ in modulating reading performance and in terms of safety and tolerability, will be a valuable step forward to identify brain-directed treatments for DD. Instead, it will be crucial to assess whether the potential comparability on behavioral outcomes will go hand in hand with comparability on tolerability and safety parameters.

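### The primary hypothesis (hf-tRNS at least as effective as tDCS) has a non-inferiority form, but the planned tests and sample size address only differences

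*Protocol article*

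**What the plan says.** The first hypothesis under Statistical analyses and expected results is that "hf-tRNS will be at least as effective as tDCS in improving TEXT reading accuracy compared with sham condition (primary outcome". Related wording appears elsewhere:

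- The abstract's Discussion: "We hypothesize that tRNS will demonstrate comparable effectiveness to tDCS in improving reading compared to sham conditions".
- The aims at the end of the Introduction link later multi-session work to this result: "If hf-tRNS proves to be at least as effective as tDCS in improving reading outcomes".
- The Conclusion says "we preferred to be cautious in advancing hypotheses of superiority of one technique over the other", while "expecting comparable effects of the two techniques on outcome measures".

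The primary outcome under Reading tasks is framed differently, as "changes in TEXT reading accuracy during the active tDCS and active hf-tRNS sessions compared to the sham session".

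The analysis is an RM-ANOVA "with conditions (Day 0, A, B, C) as a within-subjects factor and age as covariate". Partial eta squared is the effect size. For the pairwise contrasts the plan states that "comparisons will be assessed using Tukey’s honest significance test". The Sample size section gives N = 24 from f = 0.25, alpha 0.05 and 80% power for an RM-ANOVA with four repeated conditions. The article gives no margin, confidence-limit rule or equivalence test for hf-tRNS against tDCS.

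**The concern.** Claiming that one technique is at least as effective as another requires ruling out a loss larger than some stated amount. RM-ANOVA and Tukey's test can reject equality, but failing to reject it rules out nothing. The primary outcome and the primary hypothesis therefore ask different questions, and the planned tests answer only the first.

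This goes beyond detail that an article may leave to an analysis plan. The article itself fixes the hypothesis, the test, the post hoc method and N, and these do not fit together. At stake is how the hf-tRNS versus tDCS result will be interpreted. With no other rule stated for that comparison, a non-significant difference could be taken as comparability and used to support multi-session hf-tRNS protocols.

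**Working it through.** **Inputs from the Sample size section:** f = 0.25, alpha = 0.05, power 80%, m = 4 conditions, N = 24.

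**Assumptions not in the document:** correlation rho = 0.5 between conditions (range 0.3 to 0.8); sphericity; both active conditions shifted by d and baseline and sham unshifted; age covariate ignored. Effects are in units of the between-child SD of TEXT accuracy. With means (0, d, d, 0), the SD of the means is d/2, so f = 0.25 gives d = 0.5 SD.

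**1. The plan's own figure.** Noncentrality = f²·N·m/(1 − rho) = 0.0625 × 24 × 4 / 0.5 = 12, with 3 and 69 degrees of freedom. Power is 81.7%, and 24 is the smallest N reaching 80%. The stated N reproduces, but for the question of any difference among four conditions.

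**2. Precision of hf-tRNS minus tDCS.** The SD of the paired difference is √(2(1 − rho)) = 1.0 SD at rho 0.5.
- 95% CI half-width: 2.069 × 1.0/√24 = 0.42 SD.
- Tukey critical difference: q(0.95; 4, 69) = 3.723, and 3.723 × √(0.5/24) = 0.54 SD. This exceeds the whole assumed 0.5 SD effect.

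**3. Chance that Tukey finds no difference between the techniques when tDCS works (0.5 SD).** The critical t is 3.723/√2 = 2.633 on 69 df, with noncentrality δ√24/SD of the difference.
- hf-tRNS keeps half the effect (δ = 0.25): noncentrality 1.225, non-significant in 91%.
- hf-tRNS has no effect (δ = 0.5): noncentrality 2.449, non-significant in 57%.

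**4. Adding a requirement that hf-tRNS beats sham by Tukey.** This was simulated with 40,000 trials per setting; results are in the table.

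**5. Power for a non-inferiority test at N = 24.** The margin is 0.25 SD (half the assumed effect, for illustration only), one-sided alpha is 0.025 and the true difference is zero. The noncentrality is 0.25√24/1.0 = 1.225 and the critical t is 2.069 on 23 df, giving 22% power. About 128 children would be needed for 80%. The smallest margin with 80% power at N = 24 is 0.60 SD at rho 0.5 (0.71 at rho 0.3, 0.38 at rho 0.8).

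| Quantity at N = 24 | rho 0.3 | rho 0.5 | rho 0.7 | rho 0.8 |
|---|---|---|---|---|
| Half effect: techniques not significantly different | 94% | 91% | 85% | 75% |
| Half effect: as above and hf-tRNS beats sham | 6% | 8% | 15% | 23% |
| No effect: techniques not significantly different | 71% | 57% | 30% | 11% |
| No effect: as above and hf-tRNS beats sham | 0.5% | 0.5% | 0.4% | 0.3% |
| Power to exclude a 0.25 SD loss if truly equal | 17% | 22% | 33% | 46% |

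**The case against.** The strongest reply is that the hypothesis also contains a comparison with sham. The primary outcome is each active condition against sham, and Tukey's test covers that contrast. If hf-tRNS must beat sham as well as not differ from tDCS, an ineffective technique passes in about 0.5% of trials at rho 0.5. A reader might infer that the plan lets a useless technique through, or that a non-significant difference from tDCS is the only route to the claim. The sham comparison means the documents support neither.

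A reader might also infer that non-significance will be treated as equivalence. No section says so. The Conclusion is cautious and speaks of weighing the magnitude of the two effects. Nor is N = 24 an arithmetic error, since it reproduces for the test it names. The article calls the study proof-of-concept, and the active-versus-sham comparisons can be tested as planned.

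These points limit the harm but do not remove the mismatch. The article states no joint rule. Beating sham shows that hf-tRNS does something; it does not show that it does as much as tDCS. Requiring only that tDCS beats sham does not help either: in such trials at rho 0.5, a half-effective hf-tRNS still does not differ significantly from tDCS in about 83%. Partial eta squared gives no interval for the difference between techniques.

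**Conclusion.** The concern holds as a mismatch between the stated primary claim and the stated test, sample size and primary outcome. The planned analysis can address whether each active condition differs from sham. It cannot show that hf-tRNS is at least as effective as, or comparable to, tDCS.

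The most robust figure is the half-effect case, where a real loss of half the benefit goes undetected in 75% to 94% of trials across the correlations examined. The no-effect figure (11% to 71%) depends heavily on rho, so it is not safe to say that non-significance is the likely result when hf-tRNS does nothing. All figures rest on the assumed 0.5 SD effect, sphericity and correlation; the 17% to 46% power also rests on an illustrative margin. Because the sham comparison can be tested and a change of text cures the problem, this should be fixed but does not invalidate the trial.

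**What to change.** 1. State the primary hypothesis as superiority of each active condition over sham, matching the primary outcome under Reading tasks.
2. Make hf-tRNS minus tDCS a secondary estimate with a two-sided 95% confidence interval.
3. State that a non-significant difference between the techniques will not be taken as comparability.
4. Allow the wording at least as effective only if the lower confidence limit lies above a margin that is justified and fixed before unblinding, and tDCS itself beats sham. Say that N = 24 gives low power for a margin such as 0.25 SD.
5. Align the abstract, Introduction and Conclusion with this.

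The cost is a change of text and a more modest claim; no extra participants are needed for it. Keeping non-inferiority as the primary claim would instead mean resizing the trial, to about 128 children for a 0.25 SD margin at rho 0.5 (178 at rho 0.3, 53 at rho 0.8).

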### Safety, tolerability, and blinding assessment

Adverse effects will be assessed using a questionnaire adapted from Antal et al. (59). Participants will be asked to complete the questionnaire after each session. The questionnaire includes items related to potential adverse effects such as headache, tingling, skin redness, neck pain, scalp pain, itching, drowsiness, difficulty concentrating, burning sensation, and acute mood change. In addition, other information regarding when the adverse event occurred, its duration, and where the discomfort is located will be recorded. Participants will quantify the severity of adverse effects as follows: (0) absent; (1) mild; (2) moderate; and (3) severe.

The questionnaire will also inquire about participants’ perception of whether they received active stimulation or not. For more details, see Supplementary materials S4.

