### Protection of risks

To reduce any risks associated with tDCS/tRNS, participants will be closely monitored throughout the stimulation sessions and encouraged to report any discomfort. Should they experience uncomfortable scalp sensations or headaches, the stimulation will be immediately halted. All tDCS/tRNS sessions will be conducted and supervised continuously by a trained experimenter.

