### Withdrawal of subjects and intervention modifications

Any suspensions or interruptions of the treatment will be documented by the investigator. Subjects will be immediately withdrawn from the study if there are foreseeable or unforeseeable adverse effects. If withdrawal occurs during the intervention phase, the subject’s data will not be considered for analysis. Replaced subjects will be those who undergo the complete protocol.

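### The safety hypothesis claims parity with sham but defines it as zero severe events and zero intolerance dropouts under active stimulation, a rule that contains no contrast with sham

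*Protocol article*

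**What the plan says.** Under *Statistical analyses and expected results*, the third hypothesis opens: "hf-tRNS and tDCS will be as safe as sham condition (i.e., neither tDCS nor hf-tRNS will induce severe AEs or lead to dropouts". Its defining clause in full is "neither tDCS nor hf-tRNS will induce severe AEs or lead to dropouts due to intolerance to stimulation". The same section separately states: "Chi-Square analyses will be used to compare the groups on demographic and safety and blinding measures (categorical variables".

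Under *Safety, tolerability, and blinding assessment*, children complete a questionnaire after every session, sham included, and grade each effect as "0) absent; (1) mild; (2) moderate; and (3) severe".

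Two further sections bear on what counts as an event:

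- *Protection of risks*: "Should they experience uncomfortable scalp sensations or headaches, the stimulation will be immediately halted".
- *Withdrawal of subjects and intervention modifications*: "Any suspensions or interruptions of the treatment will be documented by the investigator" and "Subjects will be immediately withdrawn from the study if there are foreseeable or unforeseeable adverse effects". Data from a child withdrawn during the intervention phase are left out of the analysis, and replacements are children who complete the whole protocol.

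*Study design* gives each child one tDCS, one hf-tRNS and one sham session. *Sample size* sets 24 children, calculated on text reading accuracy only.

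**The concern.** The claim is comparative, but its definition is not. Parity with sham is a statement about a difference. The bracketed gloss is a statement about active sessions alone.

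The rule also counts only the top grade of a four-point scale. The Discussion motivates the tolerability comparison with effects that need not reach that grade: in an earlier paediatric study, 6 participants reported adverse events with tRNS against 13 with tDCS, and itching occurred in 7% against 13% of sessions. The same pattern at grades 1 and 2 would leave the criterion satisfied.

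The Discussion names the comparison of safety and tolerability among the main purposes of the study, with a view to standard-of-care use in children. A parity statement resting on this rule would carry weight that the rule cannot bear.

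**Working it through.** **1. The plan's own figure.** The article gives no figure for the safety hypothesis. Its only sample-size figure is N = 24 for the primary outcome: repeated-measures ANOVA, m = 4 levels, f = 0.25, α = 0.05, 80% power. With an assumed correlation ρ = 0.5 and ε = 1 (neither is stated), λ = f²·N·m/(1−ρ) = 0.0625 × 24 × 4 / 0.5 = 12, with 3 and 69 degrees of freedom. Power is 0.817 at N = 24 and 0.797 at N = 23, so 24 reproduces. It was not chosen for a safety claim.

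**2. Exposure.** One session per condition in 24 children gives 24 tDCS, 24 hf-tRNS and 24 sham sessions. The rule concerns the 48 active sessions and none of the sham sessions. I read a severe event as grade 3 on the questionnaire.

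**3. What zero events excludes.** Exact upper limit after 0/24 for one technique:

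- one-sided 95%: 1 − 0.05^(1/24) = 0.117
- two-sided 95%: 1 − 0.025^(1/24) = 0.142

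**4. Chance that the rule is met.** Let p be the true per-session risk of a severe event or intolerance dropout. The documents give no such rate, so every p is an assumption. For one technique the chance is (1−p)^24. The rule as written covers both techniques. With equal risks and independent events the chance is (1−p)^48, and if events within a child were fully dependent it would be (1−p)^24.

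| Assumed p | One technique, (1−p)^24 | Both, independent, (1−p)^48 |
|---|---|---|
| 1% | 79% | 62% |
| 2% | 62% | 38% |
| 3% | 48% | 23% |
| 5% | 29% | 9% |
| 10% | 8% | 0.6% |

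**5. Failure when parity is true.** If p = 2% in every condition, sham included, the active techniques are exactly as safe as sham. The rule is still violated with probability 1 − 0.98^48 = 0.62 (independent events), or 1 − 0.98^24 = 0.38 (full dependence).

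**6. What a comparison with sham could show.** With 0/24 under both active and sham, the upper 95% limit for the difference is about 14 percentage points (Wilson/Newcombe, zero within-child correlation: 3.84/(24 + 3.84) = 0.138). For a formal non-inferiority comparison (one-sided 2.5%, 80% power), n = (1.96 + 0.84)² × 2p(1−p)/margin². With an assumed 10-point margin this needs about 31 children at a 2% event rate in both conditions and about 75 at 5%. With a 5-point margin it needs about 124 and 299. The documents state no margin.

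**7. Halted sessions, section against section.** *Protection of risks* halts stimulation for scalp discomfort or headache. The safety hypothesis counts dropouts, not halts. *Withdrawal of subjects* withdraws a child for adverse effects with no severity threshold, and the questionnaire lists headache and scalp pain as adverse effects. Read literally, a halt for headache leads to withdrawal and may be an intolerance dropout, so the rule fails. If a halted child may continue, the halt is not counted. If withdrawn children's data are excluded and the child replaced, the analysed set holds no dropouts by construction. The text does not settle which applies.

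**The case against.** The strongest reply is that the protocol does plan to compare safety measures. The questionnaire covers sham and all grades, and Chi-square analyses are specified, so a reader who inferred that there is no comparison with sham at all would be wrong. That stands. What remains is that those tests are not linked to the hypothesis, which carries its own criterion. A Chi-square test for independent groups does not use the fact that the same child sits in every condition. A non-significant result in 24 children would not demonstrate parity either.

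Second, a reader might infer that halted sessions are ignored, so that several halted tDCS sessions could coexist with a parity verdict. The documents do not establish this. Interruptions are documented, and the withdrawal section can be read as turning a halt into a dropout. Nor does any text say that halting keeps effects below grade 3. Only the need for reconciliation stands.

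Third, the sentence is a hypothesis in a study that calls itself proof-of-concept, and no passage states that parity will be declared if no event occurs. That is fair and keeps the point at the level of a secondary hypothesis. The gloss nevertheless fixes what the hypothesis means.

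Fourth, tabulations by grade are commonly left to an analysis plan that is not shown. That is also true, but the definition criticised here is printed in the article.

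**Conclusion.** The point holds in limited form. The stated criterion cannot support parity with sham, because it contains no sham contrast and leaves out grades 1 and 2. This does not depend on any assumed rate.

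The size does depend on assumptions. Zero events in 24 leaves risks up to 11.7% (one-sided 95%) or 14.2% (two-sided 95%) per technique unexcluded. The rule across both techniques is met with probability about 38%, 23% and 9% at assumed risks of 2%, 3% and 5% if events are independent.

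A reader might infer that the rule would often be met despite a material risk. The documents do not support that as a general statement: they give no event rate and do not say what risk is material, and at 10% the chance is at most 8%.

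The primary sample size is not in question. The change should be made because the safety conclusion is one of the study's stated purposes.

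**What to change.** Replace the bracketed definition in the safety hypothesis. For every child stimulated, including any later withdrawn, report by condition the number of sessions halted, the number with any effect of grade 2 or higher, and the number with grade 3. For each active technique give the paired within-child difference from sham with a 95% confidence interval. If no severe effect occurs, conclude that none was observed and report 0/24 with its upper limit of about 14% (recalculated if more children are stimulated), not that the techniques are as safe as sham.

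Reconcile *Protection of risks*, *Withdrawal of subjects and intervention modifications* and the safety hypothesis, so that it is clear whether a halted session counts as an intolerance dropout and whether that child's safety data are retained.

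The cost is the rewording of one hypothesis, one clarification and one table. The data are already collected through the questionnaire and the record of interruptions. The downside is a less favourable safety statement.
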